## Abstract

**Background:**

Psychotic experiences, social functioning and general psychopathology are important targets for early intervention in individuals with Ultra-High-Risk state (UHR) and a first-episode psychosis (FEP). Acceptance and Commitment Therapy (ACT) is a promising, next-generation Cognitive Behavioural Therapy (CBT) that aims to modify these targets, but evidence on sustainable change and its underlying mechanisms in individuals’ daily lives remains limited. The aim of the INTERACT study is to investigate the efficacy of a novel ecological momentary intervention, Acceptance and Commitment Therapy in Daily Life (ACT-DL) in a multi-centre randomised controlled trial of individuals with UHR or FEP.

**Methods/design:**

In a multi-centre randomised controlled trial, individuals aged 16–65 years with UHR or FEP will be randomly allocated to ACT-DL in addition to treatment as usual (TAU) as the experimental condition or a control condition of TAU only, which will include – for the entire study period – access to routine mental health care and, where applicable, CBT for psychosis (CBTp). Outcomes will be assessed at baseline (i.e. before randomisation), post-intervention (i.e. after the 8-week intervention period), and 6-month and 12-month follow-ups (i.e. 6 and 12 months after completing the intervention period) by blinded assessors. The primary outcome will be distress associated with psychotic experiences, while secondary outcomes will include (momentary) psychotic experiences, social functioning and psychopathology. Process measures to assess putative mechanisms of change will include psychological flexibility, stress sensitivity and reward experiences. In addition, acceptability, treatment adherence and treatment fidelity of ACT-DL will be assessed.

**Discussion:**

The current study is the first to test the efficacy of ACT-DL in individuals with UHR and FEP. If this trial demonstrates the efficacy of ACT-DL, it has the potential to significantly advance the treatment of people with UHR and FEP and, more generally, provides initial support for implementing mHealth interventions in mental health services.

**Trial registration:**

Netherlands Trial Register, ID: NTR4252. Registered on 26 September 2013.

## Background

The state of Ultra-High-Risk (UHR) (also known as an At-Risk Mental State (ARMS) or High-Risk (HR) state) [1, 2] is associated with an increased risk of developing a first-episode psychosis (FEP), with meta-analytic evidence suggesting that conversion to FEP is most likely to occur within 2 years (risk estimate, 29%; 95% CI, 23–36) and to plateau from the third year after presentation to mental health services (risk estimate, 36% after 3 years, approximately 35% after 10 years) [3, 4]. This has been taken to suggest that the UHR state is temporally and phenomenologically continuous with FEP [5], together reflecting the early stages of psychotic disorder [1, 2, 5–7]. Further, social functioning of UHR individuals, who do neither convert to psychosis nor remit, has been reported to be lower than in healthy controls and remarkably similar to those who convert to psychosis [8]. It has been argued that providing an avenue for help in individuals with UHR is important to reduce distress associated with psychotic experiences and impaired functioning to prevent deterioration and persistence prior to the onset of full-blown psychotic symptoms [9]. While sustained periods of remission occur after the first onset of a psychotic disorder [10], persisting psychotic symptoms are associated with significant levels of distress [11, 12] and poor long-term functioning and social outcomes have been reported for the majority of FEP individuals [10, 13], who face a marked mortality gap compared with the general population [14].

A number of psychological mechanisms have been proposed by current aetiological models that may contribute across different phenomenological and temporal stages to the development of psychosis [15–20]. One mechanism that has been repeatedly suggested to play an important role is behavioural sensitisation, which has been posited to amplify the stress response in individuals with increased genetic and/or socio-environmental risk, such that they experience a greater response to even minor stressors and daily hassles, which, in turn, contributes to pushing them along a pathway to psychosis over time [21]. At the behavioural level, the most commonly used marker of this underlying process of behavioural sensitisation is stress sensitivity, characterised by stronger negative emotional reactions to minor stressors in daily life [22, 23]. Previous research suggests that emotional reactivity to minor stressful events, activities, and social situations is increased in individuals with UHR [23, 24] and FEP [23]. At the same time, it has been shown that deficits in reward experience are linked to motivational impairments in psychosis [25, 26].

Developing and evaluating interventions that directly modify these putative mechanisms in daily life to reduce the intensity of psychotic experiences at an early stage is a promising strategy for preventing transition to, and improving outcomes of, psychosis [23, 27–29]. Building on recent advances in the field of mobile Health (mHealth) interventions [30], we have recently proposed an ecological interventionist causal model approach for targeting psychological mechanisms in daily life [29]. This approach draws on ecological momentary interventions (EMIs) (as proposed by our own group [28, 29] and others [31]), which deliver real-time psychological interventions in daily life, thereby, enabling individuals to access interventions that are tailored to what a person needs in a given moment and context, with the goal of producing changes in mechanisms that lead to sustainable change in intended outcomes under real-world conditions [29].

While the initial evidence suggests that psychological interventions such as Cognitive Behavioural Therapy (CBT) may be efficacious in reducing transition rates in individuals with UHR, there is still only a small number of methodologically robust studies to investigate this issue, and evidence on sustainable change in relation to distress associated with symptoms, social functioning as well as the above-mentioned psychological mechanisms remains very limited [32–34]. Recently, there has been increasing interest in Acceptance and Commitment Therapy (ACT), which is a next-generation CBT targeting the relationship of individuals with their feelings and thoughts rather than their content, with the overarching goal of enhancing individuals’ psychological flexibility [35, 36]. ACT aims to train individuals in core psychological processes of acceptance (e.g. of unpleasant, stressful feelings and thoughts), non-judgemental contact with the present moment, values, committed action, self as context, and cognitive defusion [35, 37–39]. While ACT components targeting acceptance are likely to be effective in attenuating stress sensitivity, ACT components targeting commitment (values, committed action) are likely to enhance reward-related motivated action. There is good evidence on the feasibility and acceptability of ACT in people with psychosis [40, 41]. Initial evidence further suggests that ACT may reduce hospital re-admission rates, psychotic and affective symptoms, social impairment, and distress associated with hallucinations in this population [42–45]. While some studies have reported an effect of ACT on hypothesised mechanisms (such as experiential avoidance or belief flexibility about symptoms) [39, 40, 44], a recent RCT in people with persisting psychotic symptoms did not find an effect on targeted mechanisms, calling for improved investigation of psychological processes underlying change in distress and other outcomes [45]. Further, our understanding of whether, and if so how, therapeutic effects translate into individuals’ daily lives remains very limited.

Delivering ACT and evaluating its effects on putative mechanisms in daily life based on principles of EMIs is, therefore, both timely and eminently important. Acceptance and Commitment Therapy in Daily Life (ACT-DL) has recently been developed for enhancing the therapeutic effects of ACT under real-world conditions [28–30, 46]. ACT may be particularly amenable to be implemented as an EMI, as it emphasises the context in which a behavior occurs as well as the function of this behavior in a given context [46]. In a recently completed pilot study to evaluate the acceptability and clinical feasibility of ACT-DL in a heterogeneous clinical sample of patients with mental disorder, very good completion rates, use of exercises, and positive user experience were found [47], but there is no robust, trial-based evidence on its effects in the early stages of psychosis.

Against this background, the aim of the current study is to investigate the efficacy of ACT-DL in a multi-centre randomised controlled trial of patients with UHR or FEP (INTERACT). The manualised ACT-DL intervention will be administered to UHR and FEP patients in addition to treatment as usual (TAU) (experimental condition) and compared to a control condition of TAU only, which will be standard mental health care including Cognitive Behavioural Therapy for psychosis (CBTp) where applicable. Specifically, the study aims to:
Test the efficacy of ACT-DL on reducing distress associated with psychotic experiences at post-intervention, 6-month and 12-month follow-ups (primary outcome)Test the efficacy of ACT-DL on reducing (momentary) psychotic experiences, psychopathology, and improving social functioning (secondary outcomes), as well as on reducing stress sensitivity and enhancing reward experience and psychological flexibility (process measures to assess mechanisms of change) at post-intervention, 6-month, and 12-month follow-upsExamine, consistent with established credibility criteria [48], the effects of ACT-DL in UHR compared with FEP individuals in a priori planned subgroup analysesAssess the acceptability, treatment adherence and treatment fidelity of ACT-DL in UHR and FEP patients

## Methods/design

### Study design

In a multi-centre randomised controlled trial, individuals aged 16–65 years with UHR or FEP will be randomly allocated to ACT-DL in addition to TAU as the experimental condition or a control condition of TAU only, which will include routine mental health care and, where applicable, CBTp. Participants will be recruited from mental health services in the Netherlands and Flanders, Belgium. Outcomes will be assessed at baseline (i.e. before randomisation), post-intervention (i.e. after the 8-week intervention period), and 6-month and 12-month follow-ups (i.e. 6 and 12 months after completing the intervention period) by blinded assessors (see Figs. 1 and 2, and Additional file 1 in Supplementary information). Randomisation will be conducted by an independent researcher through a computer-generated sequence. All outcomes will be assessed and all statistical analyses will be conducted blind to treatment allocation.

**Fig. 1 Fig1:**
[figure not shown]
Anticipated study flowchart

**Fig. 2 Fig2:**
[figure not shown]
Standard Protocol Items: Recommendations for Interventional Trials (SPIRIT) Figure

### Participants

The study will aim to recruit 150 participants with UHR or FEP from secondary mental health services at clinical sites of five centres: (1) Amsterdam (Academic Medical Centre, Arkin Basis GGZ), (2) The Hague (Parnassia/PsyQ), (3) Maastricht/Eindhoven (Mondriaan, Virenze, GGZE) (all in the Netherlands), (4) Flemish-Brabant (Leuven (UPC KU Leuven), Antwerp (VDIP), Diest (Sint-Annendael), Mortsel (PCM)), and (5) East/West Flanders (Brugge (OLV), Melle (Karus), Sint Niklaas (VDIP)) (all in Belgium). Individuals receiving care from these secondary mental health services will be approached by a clinician of these services, who will provide initial information about the study. Individuals, who are interested to take part in the study, will be asked for their consent to be approached by a member of the research team to learn more about the study. If the potential participant agrees, they will be fully informed about the study in a face-to-face session or on the phone by a researcher and, after 1 week, asked for written informed consent. Full eligibility assessment will be conducted by the researcher once participants have provided written informed consent, which can be withdrawn at any time without any negative consequences for participants. Participants will be rewarded financially for complete participation, and travel expenses will be fully reimbursed.

#### Inclusion criteria

The inclusion criteria are as follows: (1) aged 16–65 years; (2) an UHR (without prior use of antipsychotic medication) or FEP (onset within last 3 years) as assessed by the Comprehensive Assessment of At Risk Mental State (CAARMS) [1] and Nottingham Onset Schedule (NOS) [49]; (3) sufficient command of the Dutch language to follow instructions for assessment of outcomes and receiving the intervention; and (4) ability to provide written informed consent.

#### Exclusion criteria

The exclusion criteria are as follows: (1) a primary diagnosis of alcohol/substance abuse and dependence, assessed with the Mini-International Neuropsychiatric Interview (MINI) [50]; and (2) severe endocrine, cardiovascular or brain disease.

### Interventions

#### Control condition: treatment as usual (TAU)

Participants allocated to the treatment as usual (TAU) control condition will continue to receive all the treatment they received prior to the start of the study. This will include good standard care delivered according to local and national service guidelines and protocols by their general practitioner, psychiatrist and other members of the mental health care team. Standard mental health care will include CBTp at some sites, which will be assessed together with other service contacts using a service-use checklist to monitor variation in the delivery of mental health services and allow for planned subgroup analysis.

#### Experimental condition: ACT-DL + TAU

Participants allocated to the experimental condition will receive ACT-DL with trained clinicians within an 8-week period in addition to TAU, which will consist of all the treatment that they received prior to the start of the study and include all the input from their general practitioner, psychiatrist, and other members of the mental health care team that they would receive if they did not participate in the study, with the exception of manualised CBTp. The intervention can be discontinued by participants at any time upon request without any negative consequences.

The manualised ACT-DL intervention consists of eight ACT training sessions (including one session for psychoeducation) administered face-to-face by a trained clinician (i.e. psychologists having received a 5-day training in ACT-DL and receiving fortnightly supervision sessions for the purposes of the trial), each for around 45–60 min, and an ACT-based EMI, which participants will receive following randomisation to the experimental condition [46], over an 8-week intervention period. The latter will be administered through a smartphone-based app (i.e. the PsyMate™ app) to allow participants to apply the skills that they have been trained into their daily lives [28–30]. The first six face-to-face ACT sessions are based on a modified version of ACT for people with psychosis [35, 43, 44, 51] and aim to enhance participants’ psychological flexibility by training them in six core components: creative hopelessness, acceptance, cognitive defusion, self as context and contact with the present moment, values, and committed action [46, 52]. In the last session, all six components will be integrated and reviewed.

The ACT-based EMI will train participants in applying the ACT techniques and skills from the sessions to their daily life through exercises and metaphors focussing on the six ACT components without involvement of the trained clinician on at least three consecutive days per week following (from session 2) each face-to-face session. On each of these days, participants receive prompts on the app at eight semi-random moments, asking them to complete a brief questionnaire on their current mood, psychotic experiences and activities, with the goal of increasing awareness of their current psychological state. Participants are then offered either an ACT exercise or metaphor training them in the ACT component covered in the face-to-face session. After participants are trained in each ACT component separately, the EMI is extended to cover the full range of components in order to train participants to flexibly adopt ACT skills and techniques depending on the context. In addition, participants are asked to apply skills and techniques in situations when they are most needed (e.g. at times of distress associated with psychotic experiences, during challenging activities or situations). After completion of the intervention period, participants will no longer have access to the app. Please see Steinhart et al. [46] for a more detailed account of the ACT-DL intervention.

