### Statistical analysis

The investigators will access the final trial dataset to test the primary hypothesis of a reduction in distress associated with psychotic experiences measured with the CAARMS using a linear regression model with distress at all three time points (i.e. post-intervention, 6-month and 12-month follow-ups) as the dependent variable and distress at baseline, condition (ACT-DL + TAU vs. TAU), time (as a three-level factor), centre (as a five-level factor), the baseline × time interaction, and the condition × time interaction as independent variables, according to the intention-to-treat principle. Within-subject clustering of repeated measures will be taken into account by allowing residuals within subjects to be correlated with a completely unstructured variance-covariance matrix.

The model will be fitted using restricted maximum likelihood estimation using Stata 15 [85]. This will allow for the use of all available data under the assumption that data is missing at random and if all variables associated with missing values are included in the model [86, 87]. Hence, bias due to attrition over time, due to difference between groups, or as a function of baseline distress is already mitigated by the model. Potential bias due to missing outcomes will be assessed in descriptive analyses of baseline characteristics stratified by missing data for the primary outcome and condition as follows: (a) experimental condition with no missing primary outcome at post-intervention time point, (b) experimental condition with missing primary outcome at post-intervention time point, (c) control condition with no missing primary outcome at post-intervention time point, and (d) control condition with missing primary outcome at post-intervention time point [88, 89].

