The main effect of condition will be tested via an omnibus test of no difference between the two conditions at all three time points (Wald-type test with df = 3 and alpha = .05). Should the omnibus test be statistically significant, then the three time-specific contrasts will be examined to determine at which time points significant differences are present (each tested at alpha = .05). Secondary hypotheses and analyses of process measures to assess putative mechanisms of change will be tested following the same steps. Given that block randomisation will be carried out in blocks of six participants, with stratification for centre and group, all analyses will include centre and group as covariate, even though there is little reason to expect noteworthy clustering of outcomes by centre.

In addition, multilevel mediation analysis will be used to test indirect effects of condition on primary outcomes (distress associated with psychotic experiences) and secondary outcomes (psychotic experiences, psychopathology, social functioning) via pathways through putative mechanisms of change (psychological flexibility, stress sensitivity, reward experience). Multilevel mediation models will be fitted in MPlus, Version 7 [90], to control for within-subject clustering of multiple time points [91, 92], using the MLR estimator, which allows for the use of all available data under the assumption that data is missing at random (if all variables associated with missing values are included in the model). In a two-level model, multiple time points (level 1) will be treated as nested within subjects (level 2). The total effect of condition (level 2) on primary/secondary outcomes (level 1) will be apportioned into direct and indirect (or, synonymously, mediating) effects through putative mechanisms of change (level 1) using the product of coefficients strategy. This strategy quantifies the point estimate of the indirect effect as the product of the coefficient of independent variable on mediator variable (path a) and the coefficient of mediator variable on dependent variable (path b). We will use statistical software by Selig and Preacher [93] for computing Monte Carlo confidence intervals and assessing the statistical significance of indirect effects, given their advantages over rival methods in the context of multilevel mediation models [93, 94].

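### ACT-DL therapists treat one arm only, and the primary model has no therapist term: if therapists differ, the standard error of the condition effect is too small

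*Protocol article*

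**What the plan says.** Under Experimental condition, the article states: "The manualised ACT-DL intervention consists of eight ACT training sessions". Each lasts about 45 to 60 minutes and is "administered face-to-face by a trained clinician", meaning a psychologist with five days of ACT-DL training and supervision every two weeks. An app-based component runs alongside. Under Control condition, participants carry on with their existing care and have no ACT-DL therapist.

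Statistical analysis writes the primary model out. The terms are baseline distress, condition, time, centre, baseline × time and condition × time, and group is added as a covariate further on. The only correlation allowed is within a participant: "Within-subject clustering of repeated measures will be taken into account by allowing residuals within subjects to be correlated with a completely unstructured variance-covariance matrix". The test of condition is specified as "Wald-type test with df = 3 and alpha = .05".

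Clustering between participants is mentioned once, for centre, which is included "even though there is little reason to expect noteworthy clustering of outcomes by centre". The mediation models stop at the participant level, and so do the experience-sampling models. The Sample size section states no ICC or design effect.

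**The concern.** This is a partially nested design: participants in one arm share therapists and those in the other do not. If some therapists obtain better results than others, the outcomes of participants treated by the same person are positively correlated. The stated model treats all participants as independent given the covariates.

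Centre does not repair this. It enters as a main effect common to both arms and is not crossed with condition, so it cannot absorb variation that exists only among ACT-DL participants.

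At stake is the error rate of the primary test. With any positive therapist ICC and more than one participant per therapist, the interval for the condition effect is too narrow and the nominal 0.05 is exceeded. The article itself treats the therapist's contribution as worth measuring: it collects working-alliance ratings from clinicians and patients, and rates fidelity from session recordings.

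**Working it through.** **Inputs from the article.** 150 randomised, 75 per arm; 31% attrition; d = 0.5; alpha 0.05; 3 df; stated power 0.92. Analysed: 150 × 0.69 = 103.5, given as 104, so n = 52 per arm.

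**Assumptions (not in the article).** Baseline–outcome and between-visit correlations all 0.5; d = 0.5 at all three visits; K therapists with equal caseloads 52/K; ICC = therapist variance as a share of total unadjusted outcome variance (set to 1); therapist effect constant over time.

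**The plan's own power first.** After baseline adjustment the outcome covariance has 1 − 0.5² = 0.75 on the diagonal and 0.5 − 0.5² = 0.25 off it.
- Variance of one time-specific contrast: 0.75 × 2/52 = 0.02885.
- Row sum of the contrast covariance: (0.75 + 0.25 + 0.25) × 2/52 = 0.04808.
- Noncentrality: 3 × 0.5² / 0.04808 = 15.6. Power of the 3-df test: 0.928.

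This is close to 0.92, but other correlations and effect patterns gave about 0.63 to above 0.99. The stated figure is therefore attainable without any therapist effect, but it does not follow from the stated inputs alone.

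**Adding therapists.** Every element of the true contrast covariance rises by a = ICC × (1/K − 1/52). Then:
- true SE / model SE = √(1 + a/0.02885);
- size = P(λχ²₁ + χ²₂ > 7.815), with λ = 1 + 3a/0.04808;
- noncentrality with the correct variance = 0.75 / (0.04808 + 3a).

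*Example, K = 13, ICC 0.05.* a = 0.05 × (0.07692 − 0.01923) = 0.00288. SE ratio = √1.10 = 1.05. λ = 1.18, size 0.061. Noncentrality = 0.75/0.05673 = 13.2, power 0.88.

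K = 13 corresponds to one therapist per service listed under Participants (2 + 1 + 3 + 4 + 3, counting Parnassia/PsyQ as one). K = 5 would be one per centre.

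| K | ICC | SE ratio | Size at nominal 0.05 | Power, correct variance |
|---|---|---|---|---|
| 5 | 0.02 | 1.06 | 0.064 | 0.86 |
| 5 | 0.05 | 1.15 | 0.088 | 0.76 |
| 5 | 0.10 | 1.275 | 0.131 | 0.61 |
| 10 | 0.02 | 1.03 | 0.056 | 0.90 |
| 10 | 0.05 | 1.07 | 0.066 | 0.86 |
| 10 | 0.10 | 1.13 | 0.084 | 0.78 |
| 13 | 0.02 | 1.02 | 0.054 | 0.91 |
| 13 | 0.05 | 1.05 | 0.061 | 0.88 |
| 13 | 0.10 | 1.10 | 0.074 | 0.82 |
| 20 | 0.02 | 1.01 | 0.052 | 0.92 |
| 20 | 0.05 | 1.03 | 0.056 | 0.90 |
| 20 | 0.10 | 1.05 | 0.062 | 0.87 |

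The power column treats the variances as known, so it is somewhat optimistic when K is small.

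**Does the centre factor help?** A simulation with therapists nested in five centres, centre as a fixed effect and an exact F test (8,000 replicates) rejected a true null at 0.053 / 0.092 / 0.138 with 5 therapists and 0.045 / 0.069 / 0.084 with 10, at ICC 0 / 0.05 / 0.10. These agree with the table, so the inflation survives the adjustment.

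**The case against.** The strongest reply is that the harm is conditional and may be small. The treatment is manualised, clinicians are trained and supervised, fidelity is checked, and the app exercises are done without the clinician. All of this favours a low ICC. The sizes near 0.09 and 0.13 need about five therapists, whereas thirteen services across two countries make a larger number plausible; at K = 20 and ICC 0.02 the size is 0.052. This stands, and it is why the point is put conditionally. It does not show that the ICC is zero.

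A second reply is that a condensed article may leave sensitivity analyses to the analysis plan. That is fair for the sensitivity analysis, but the article itself fixes the covariance structure and the test. Its remark about centre is not a misstatement; it simply concerns a different source of clustering.

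A reader might infer more than the article supports:
- *That the type I error does exceed 0.05, for the primary and every secondary outcome.* This needs a positive ICC, which the article neither gives nor rules out. The calculation covers the primary test only, not the secondary outcomes or the three-level experience-sampling models.
- *That the sessions are one-to-one.* The article says face-to-face, not individual. Group delivery would add clustering.
- *That the result would hold for these therapists only.* Leaving therapist out as a random factor limits formal generalisation, but it does not invalidate the comparison within the trial.

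**Conclusion.** The concern holds in conditional form. ACT-DL therapists exist in one arm only, the stated primary model has no term for them, and centre and group main effects cannot take their place. Given any positive therapist ICC with shared caseloads, the direction is certain: standard error too small, size above 0.05.

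The amount is not fixed by the article. Under the assumptions above, the true standard error is about 1% to 27% larger than reported and the size is about 0.05 to 0.13. The effect is minor with many therapists and a low ICC, and material with roughly one therapist per centre and an ICC of 0.05 or more. The plan should be changed for this, but it is no reason to discount the trial's design.

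**What to change.** Record the treating ACT-DL therapist for each participant. Pre-specify a partially nested version of the primary model: the same fixed effects and within-participant covariance, plus a therapist random effect in the ACT-DL arm only, with small-sample degrees of freedom. Treating control participants as singletons is an approximation, because they too may share clinicians, teams or CBTp providers.

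At the least, make this a sensitivity analysis for the primary outcome, report it beside the main result with the estimated ICC and the number of therapists, and interpret the efficacy claim in its light. It need not be a second test that efficacy has to pass.

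The cost is one identifier, one variance component and some wording, with no extra patients or staff. The price is statistical. Intervals widen, and at ICC 0.05 power falls from 0.93 to about 0.88 with 13 therapists or 0.76 with 5. With few therapists the variance component will be estimated imprecisely, and the report should say so.
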